### Sample size

For the calculation of the sample size, the primary endpoint of the study (shoulder pain intensity at rest measured by VAS) was considered to be directly related to the intervention and has been widely used for this purpose. The calculation was performed considering a level of significance (alpha) of 0.05 and an 80% study power, considering a clinically important difference of ≥ 3 points on the VAS [46]. Based on the results of a pilot study involving 10 individuals with PSSP (five for the active group and five for the sham), the difference between the means was 3.0 in the group submitted to physical therapy, and active tDCS and 1.56 in the submitted group to physical therapy and sham ETCC, with a combined standard deviation of 1.38, the required sample size was 22 subjects (11 per group). Taking into account the possibility of dropouts, the sample was increased by 20% to ensure a sample size that enables us to demonstrate the effect of the intervention, leading to 13 individuals in each group (total of 26 participants). This calculation was performed using the G*Power software.

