### Randomization

The allocation of the participants to the different groups will occur using a simple lottery procedure. Treatment codes (active or sham stimulation) will be placed in opaque envelopes [47, 48]. A researcher not involved in the evaluations or treatment will be responsible for the random allocation of the participants to two groups: 1) active tDCS combined with physical therapy for the upper limbs using a “mini-bike”; or 2) sham tDCS combined with physical therapy for the upper limbs using a “mini-bike”.

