#### Data analysis

Descriptive data and characteristics of the patients (gender, age, initial score on the VAS, ischemic or hemorrhagic stroke, right/left hemisphere lesion, time with pain, injury time, Fugl-Meyer upper limb score, BDI, use of controlled medications, and associated comorbidities) will be represented by mean and standard deviation or median and interquartile range. The normality of the data from the VAS, DASH, Fugl-Meyer, SSQOL, range of motion passive shoulder, and hand grip strength will be analyzed by the Shapiro-Wilk test.

If the normality hypothesis is accepted, the analysis of variance (ANOVA) followed by the Bonferroni test will be used, when necessary, to perform the comparison analysis between groups. If the normality hypothesis is rejected, the Kruskal-Wallis test will be used. The Mann-Whitney test will be used to compare the results of the study treatment periods (pre- and post-treatment and 30-day follow-up). Pearson or Spearman correlation coefficients will be calculated to determine the strength of correlations between pain and secondary outcomes (SPADI, Fugl-Meyer, SSQOL, passive shoulder range of motion and grip strength). A value of *p* < 0.05 will be considered indicative of statistical significance. All analyses will be processed using the SPSS program (IBM SPSS Statistics for Windows, Version 22.0, released in 2013, IBM Corp., Armonk, NY, USA).

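### The VAS comparison is a normality-tested switch between ANOVA and Kruskal-Wallis that names no baseline covariate and leaves the ANOVA type open; one prespecified baseline-adjusted ANCOVA would be more precise at almost no cost

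*Protocol article*

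**What the plan says.** The Data analysis section says that the distribution of the VAS and the other listed outcomes "will be analyzed by the Shapiro-Wilk test". If normality is accepted, "analysis of variance (ANOVA) followed by the Bonferroni test will be used, when necessary, to perform the comparison analysis between groups". If it is rejected, Kruskal-Wallis is used. The next sentence assigns Mann-Whitney to the comparison of the three time points. A p-value below 0.05 "will be considered indicative of statistical significance"; sidedness is not given.

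The initial VAS appears in that section only among the descriptive characteristics. The one covariate in the article is the Beck Depression Inventory score, and it is tied to motor recovery, not to pain. VAS is measured before treatment, after the ten sessions and 30 days later, and the Pain intensity section makes pain at rest the measure that counts.

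The Sample size section reports that in the pilot "the difference between the means was 3.0 in the group submitted to physical therapy, and active tDCS and 1.56 in the submitted group" given sham, "with a combined standard deviation of 1.38". Under Randomization, "The allocation of the participants to the different groups will occur using a simple lottery procedure"; no balancing on baseline pain is described.

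**The concern.** The sizing gives one figure per arm, which is most naturally a mean improvement from baseline. The analysis text never says that change is analysed or that baseline VAS enters the model. The single word ANOVA covers several different tests: a one-visit comparison, a comparison of changes, a group main effect over three visits, or a group-by-time interaction. Their power differs widely.

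The non-normal branch is the clearer weakness. Kruskal-Wallis and Mann-Whitney are tests for independent samples. As written, nothing in that branch uses each patient's own baseline. The result of a weak pre-test can therefore change both the hypothesis tested and whether within-patient information is used at all.

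At stake is precision in a trial of 26 patients, and whether a reader can tell in advance which test is the primary one. The article itself states the tests and the switching rule, so this is not a detail left to an analysis plan that is not shown.

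**Working it through.** **Inputs.** From Sample size: "level of significance (alpha) of 0.05 and an 80% study power"; difference 3.0 − 1.56 = 1.44; SD 1.38; 11 per arm, 13 per arm randomised. Assumptions: two-sided testing; correlation ρ between VAS at different visits from 0.3 to 0.8, equal for all pairs of visits; equal SD at each visit; and, where both post-baseline visits are used, the same 1.44 effect at each. The article does not say whether 1.38 is the SD of change or of a single score, so both readings are shown.

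**The plan's own figure.** The article reports that "the required sample size was 22 subjects (11 per group"). With d = 1.44/1.38 = 1.043, a two-sided t-test needs 16 per arm. A one-sided normal approximation gives 12 per arm. A repeated-measures between-group setting with three occasions, f = d/2 = 0.52 and ρ = 0.5 gives exactly 22 in total (power 81%). So 22 is reached exactly only under a setting that the article does not declare. That is a separate sample-size matter; here it shows only that the sizing does not settle which ANOVA is meant.

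**Formulas** (noncentral t, noncentrality (effect/SD) × √(n/2), df 2n − 2, one fewer for ANCOVA):
- SD of change = SD × √(2(1 − ρ)), where SD is that of a single score
- ANCOVA residual SD = SD × √(1 − ρ²)
- Group main effect over three visits: effect 1.44 × 2/3 = 0.96, SD × √((1 + 2ρ)/3)
- Group-by-time over three visits: F on 2 and 40 df, noncentrality (n/2) × 1.44² × (2/3) / (SD²(1 − ρ))
- ANCOVA of the mean of the two post-baseline visits: residual SD = SD × √((1 + ρ)/2 − ρ²)

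**Example.** Change score: 1.043 × √5.5 = 2.45 on 20 df, power 64%. ANCOVA at ρ = 0.5: residual SD 1.38 × √0.75 = 1.195; 1.44/1.195 × √5.5 = 2.83 on 19 df, power 76%.

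**Power at 11 per arm, if 1.38 is the SD of change**

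| Analysis | ρ 0.3 | 0.5 | 0.7 | 0.8 |
|---|---|---|---|---|
| Change score | 64% | 64% | 64% | 64% |
| Group-by-time, 3 visits | 68% | 68% | 68% | 68% |
| Post score only | 79% | 64% | 44% | 31% |
| Group main effect, 3 visits | 71% | 48% | 27% | 18% |
| ANCOVA, post visit | 82% | 76% | 71% | 69% |
| ANCOVA, mean of 2 visits | 96% | 91% | 85% | 82% |

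**Power at 11 per arm, if 1.38 is the SD of a single score**

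| Analysis | ρ 0.3 | 0.5 | 0.7 | 0.8 |
|---|---|---|---|---|
| Change score | 50% | 64% | 85% | 96% |
| Group-by-time, 3 visits | 53% | 68% | 89% | 98% |
| Post score only | 64% | 64% | 64% | 64% |
| Group main effect, 3 visits | 57% | 48% | 41% | 38% |
| ANCOVA, post visit | 68% | 76% | 90% | 97% |
| ANCOVA, mean of 2 visits | 87% | 91% | 97% | over 99% |

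At 13 per arm and ρ = 0.5, change or post scores give 72% and ANCOVA of the post visit 84%.

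**Variance ratios.** ANCOVA against change score is (1 + ρ)/2: 0.65, 0.75 and 0.90 at ρ = 0.3, 0.5 and 0.8. Against the post score it is 1 − ρ²: 0.91, 0.75 and 0.36.

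**Baseline imbalance.** The standard error of the baseline difference is √(2/11) = 0.426 SD at 11 per arm and √(2/13) = 0.392 SD at 13. The chance of a difference above 0.5 SD in either direction is 24% and 20%.

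**Normality test.** In simulation with 11 values, Shapiro-Wilk at 0.05 rejects about 50% of the time for exponential data, 28% for a lognormal with log-SD 0.5, and 17% for a normal with mean 2 and SD 2 floored at 0. With 13 values the figures are about 59%, 34% and 20%. Failure to reject says little about normality at this size.

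**The case against.** The strongest reply is that the text says only ANOVA. With three visits and Bonferroni follow-up, a group-by-time analysis is a natural reading, and it already uses each patient's baseline. On the SD-of-change reading it has about 68% power, so ANCOVA of the post visit gains 8 points at ρ = 0.5, 3 at 0.7 and almost nothing at 0.8. The single contrast of both post-baseline visits against baseline, SD × √(1.5(1 − ρ)), gives 77%, no worse than one-visit ANCOVA from ρ = 0.5 upwards. This stands. Compared like with like, however, ANCOVA of the two-visit mean gives 91% and 85% at ρ = 0.5 and 0.7 against that 77%.

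Several stronger readings are tempting, but the article does not support them:
- A reader might infer that the primary analysis is definitely unadjusted, with power of 44% or 27%. Those figures belong to the post-score and main-effect readings at ρ = 0.7, which the wording allows but does not select.
- A reader might infer bias. Randomisation keeps an unadjusted comparison valid; the loss is precision.
- A reader might call imbalance likely. A chance of 20% to 24% is a real risk, not a likelihood, and adjustment deals only with baseline VAS.
- A reader might say the test is picked at will once outcomes are seen. The switch is a stated rule; the objection is that it is a weak one. No inflation of type I error has been shown.
- A reader might assume that patients with a missing visit are dropped. The article does not say so.

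The rank tests might also be meant for change scores, in which case baseline would be used. The text does not say that.

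**Conclusion.** The point holds as a free improvement. The stated method is valid, but it is loosely fixed and less precise than a baseline-adjusted model using the same data. ANCOVA is more precise than either the change score or the post score at the same visit for any correlation strictly between 0 and 1; at 11 per arm and ρ = 0.5 it gives 76% against 64%. The gain is not uniform. Over change scores at 11 per arm it runs from 18 points (64% to 82%) at ρ = 0.3 down to about 4 or 5 at ρ = 0.8 if 1.38 is the SD of change, and from 18 points (50% to 68%) down to about 1 if it is the SD of a single score. Over a three-visit group-by-time test it can be small.

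These figures rest on two-sided testing, an assumed ρ, equal SDs and correlations across visits, and an unresolved meaning of 1.38. That the sizing is on change is an inference from its wording.

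**What to change.** Prespecify one primary analysis: ANCOVA of post-intervention rest VAS on arm, with baseline rest VAS as covariate. A longitudinal model of the two post-baseline visits with baseline VAS as covariate is an acceptable alternative, provided the primary time point or contrast is named. Report the adjusted difference with its 95% confidence interval. Drop the Shapiro-Wilk switch and keep a rank-based analysis of change as a fixed sensitivity analysis. State sidedness and which SD the 1.38 is.

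The cost is wording and one degree of freedom; no new data are needed. The article was published in March 2019 and expected completion in November 2018, so if outcome data have already been unblinded, the change must be declared as made after that point.

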### Data collection, management, and analysis

All evaluations will be performed prior at baseline (preintervention), after the 10 treatment sessions (postintervention), and 30 days after the end of the treatment sessions (follow-up).

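### Mann-Whitney, a test for independent samples, is prescribed for comparing visits within the same patients; the p-values for change over time come out too large and power is lost

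*Protocol article*

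**What the plan says.** The Data analysis section of the protocol article sets out the comparisons in three steps.

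- If normality is accepted, ANOVA followed by Bonferroni "will be used, when necessary, to perform the comparison analysis between groups".
- For data that fail the Shapiro-Wilk check, the rule reads: "If the normality hypothesis is rejected, the Kruskal-Wallis test will be used".
- On the visits, the section then adds: "The Mann-Whitney test will be used to compare the results of the study treatment periods (pre- and post-treatment and 30-day follow-up").

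The third sentence carries no condition on normality. It follows the Kruskal-Wallis sentence, so it is most naturally read as part of the rank-based route.

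Two other sections define what is being compared. Data collection, management, and analysis says: "All evaluations will be performed prior at baseline (preintervention), after the 10 treatment sessions (postintervention), and 30 days after the end of the treatment sessions". The Randomization section describes "random allocation of the participants to two groups", active and sham. The arms are therefore independent samples, and the visits are repeated measurements on the same people. Neither Wilcoxon signed-rank nor Friedman, nor any other paired rank test, is named anywhere in the article.

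**The concern.** Mann-Whitney takes its reference distribution from two unrelated samples. Pre- and post-treatment scores from one patient normally move together, and that shared component cancels when the visits are compared. A test that ignores the pairing judges the change against more noise than is really there.

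With 11 to 13 patients per arm, a real change from baseline could often be reported as non-significant. The fault is in a rule that the article states, not in a detail that it leaves open: an analyst who follows the sentence literally runs the wrong test for this comparison.

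**Working it through.** The article states no figure on this point, so there is nothing to reproduce. The check has two parts.

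**1. Reading the sentence.** It compares periods and lists them as pre-treatment, post-treatment and follow-up. The comparison between arms has already been given to ANOVA or Kruskal-Wallis in the two sentences before it. With two arms, Kruskal-Wallis is equivalent to Mann-Whitney, so reading the third sentence as an arm comparison would name the same rank test twice. The natural reading is a comparison of visits within patients.

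**2. Size of the effect.**

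Inputs from the article:
- 11 evaluable patients per arm, and 13 enrolled (Sample size).
- Level 0.05 (Sample size), taken here as two-sided.

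Assumptions, because the article gives no values:
- Within-patient correlation ρ between visits, from 0 to 0.8.
- A change of 0.8 SD (or 1 SD where stated) for power.
- Normal scores with equal variance at both visits.

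*Direction, by approximation.* The difference between two visit means has true variance 2σ²(1 − ρ)/n. An independent-samples test works as if it were 2σ²/n. The true rejection rate under no change is then roughly 2[1 − Φ(1.96/√(1 − ρ))]:
- ρ = 0.3: 1.96/0.837 = 2.34, about 1.9%.
- ρ = 0.5: 1.96/0.707 = 2.77, about 0.6%.
- ρ = 0.7: 1.96/0.548 = 3.58, about 0.03%.

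Any positive ρ pushes the rate below 5%. The approximation ignores small-sample behaviour, so the sizes below come from simulation.

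*Simulation.* Bivariate normal pairs, n = 11. Mann-Whitney error rates, and both power columns, use about 20,000 simulated data sets per setting; some signed-rank error rates use 4,000.

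| Assumed ρ | Mann-Whitney type I error (nominal 5%) | Mann-Whitney power, 0.8 SD | Signed-rank power, 0.8 SD |
|---|---|---|---|
| 0 | about 5% | about 38–40% | not tabulated |
| 0.3 | about 2% | about 38–40% | 48% |
| 0.5 | about 1% | about 38–40% | 61% |
| 0.7 | about 0.2% | about 38–40% | 84% |
| 0.8 | below 0.1% | about 38–40% | 95% |

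Over ρ from 0 to 0.9 and n = 11 or 13, signed-rank kept a type I error of about 4.1–5.3%.

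The same pattern holds at n = 13 for a 1 SD change: Mann-Whitney 69% against signed-rank 89% at ρ = 0.5, and 73% against 98% at ρ = 0.7. At ρ = 0 the paired test has no advantage; with n = 11 and a 1 SD change the figures are 58% for Mann-Whitney and 51% for signed-rank. The loss therefore depends on visits being correlated, which is the usual situation for repeated scores in one patient.

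**The case against.** **The sentence may be loose wording for a comparison of the arms at each visit.** Three periods cannot enter one two-sample test, and the trial has exactly two arms. This is possible, but it is the less natural reading, because the arm comparison was already assigned and the sentence names the periods as what is compared. Either way the sentence needs rewriting.

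**The figures rest on assumptions and on normal scores.** This stands. The correlations and the 0.8 SD change are not in the article, and the sentence most likely belongs to the route taken when normality is rejected. The simulation shows the direction and rough size for normal scores; it does not predict this trial's data. Nor is it known that the pain score will take the rank-based route: a bounded scale may depart from normality, but the Shapiro-Wilk test has little power in small samples.

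Three stronger conclusions are tempting and are not supported:

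- *That the error produces false claims of improvement.* With positive correlation it does the opposite: rejection falls below the nominal level.
- *That no test in the rank-based route answers whether tDCS works.* Kruskal-Wallis on two randomised arms is a valid comparison, even on post-treatment values. The article does not say whether it is applied to visit values or to change. The Sample size section reports from the pilot that "the difference between the means was 3.0 in the group submitted to physical therapy, and active tDCS"; for the sham arm it gives "1.56 in the submitted group to physical therapy and sham ETCC, with a combined standard deviation of 1.38". Both can be read as change within each arm. Kruskal-Wallis on change would then be the comparison wanted, and the choice of variable may be fixed in an analysis plan that is not shown.
- *That naming Kruskal-Wallis for two groups is itself an error.* It is redundant but valid.

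**Conclusion.** The point holds in a limited form. On its natural reading, the Data analysis section assigns an independent-samples test to repeated measurements on the same patients and names no paired alternative. The consequence is conservative p-values and lost power for comparisons over time. At assumed correlations of 0.5 to 0.8 with 11 patients, the actual error rate is about 1% down to below 0.1%. Power for an assumed 0.8 SD change is then about 38–40%, where a paired rank test would have 61% to 95%. At lower correlation the loss is smaller, and at zero correlation it disappears.

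The randomised comparison between arms is not made invalid. What is left open there is narrower: the text does not state that the rank-based arm comparison uses change from baseline.

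**What to change.** Replace the Mann-Whitney sentence with: 'If a rank-based analysis is used, visits within patients will be compared by the Friedman test and Wilcoxon signed-rank tests, as description only; the arms will be compared by Mann-Whitney on change from baseline (post minus pre, follow-up minus pre), and only this comparison will support a claim of tDCS efficacy.'

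Removing Kruskal-Wallis is optional tidying. The last clause also prevents an efficacy claim based on a significant change in one arm and a non-significant change in the other.

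The cost is analysis wording only: no extra patients, visits or data, and the tests are available in the named software. The change should be recorded before the data are analysed, since a replacement test chosen after seeing results would be post hoc.

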Considering the relationship between pain and motor performance and the fact that long periods of cortical stimulation can have lasting effects on brain function, such as an increase in the intrinsic plasticity of the motor sensory system and the enhancement of the effectiveness of other therapeutic tools, it is believed that the combination of tDCS and physical therapy may lead to a reduction in pain. This combined therapy is expected to enhance the motor performance of patients with PSSP as well as improve both sleep quality and quality of life. Indeed, stimulation is effective at relieving a number of chronic pain conditions, especially in patients who are resistant to drug therapy [26, 40].

Therefore, the aim of the proposed study is to evaluate the effect of tDCS, when combined with upper limb physical therapy, on pain level and functional improvements in stroke patients with hemiplegic shoulder pain. As a secondary endpoint, we intend to correlate the analgesic effects of tDCS therapy and upper limb physical activity with the effects on motor performance and determine the influence of this therapeutic modality on sleep quality and quality of life.

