### Pain intensity

Pain intensity will be measured using the VAS, which consists of a horizontal straight line measuring 10 cm, with 0 cm corresponding to the absence of pain and 10 cm corresponding to maximum pain [46, 49]. The interobserver and intraobserver reliability of this measure have been demonstrated using the intraclass correlation coefficient (ICC; 0.96 to 0.98) [49]. The assessments will be performed with the patient at rest (lying down) as well as during the active (performed by the subject) and passive movements (performed by the researcher) of the painful upper limb on three occasions: preintervention, postintervention, and 30-day follow-up. The intensity of the pain to be considered will be the pain at rest, without movement.

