### Motor performance, upper limb function

The motor performance of the upper limb and its functioning will be evaluated on three occasions (preintervention, postintervention, and 30-day follow-up) using the measures below.

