### Shoulder Pain and Disability Index (SPADI)

The SPADI is a questionnaire used to measure dysfunction and disability associated with shoulder pain [50]. The numerical version of the SPADI consists of 13 items, five of which address pain and eight of which address function. Each item is scored on a numerical scale from 0 to 10 points. For the final score, the points are converted into a percentage value (0 to 100%), with higher scores denoting worse shoulder dysfunction. The SPADI has been validated for use in the Brazilian population, with excellent test-retest reliability (ICC = 0.90 to 0.94) [50], and has been used in previous studies involving stroke survivors [51].

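### The planned correlation of pain with SPADI is partly built in, because 5 of the 13 SPADI items measure shoulder pain

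*Protocol article*

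**What the plan says.** All references are to the protocol article.

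- **Aim (Background).** The authors state that "we intend to correlate the analgesic effects of tDCS therapy and upper limb physical activity with the effects on motor performance". This concerns effects, so it reads most naturally as change in pain against change in motor performance.
- **Analysis (Data analysis).** Pearson or Spearman coefficients are planned "to determine the strength of correlations between pain and secondary outcomes (SPADI, Fugl-Meyer, SSQOL, passive shoulder range of motion and grip strength"), with p < 0.05 as the significance level. SPADI is listed without restriction to any part of it.
- **Role of SPADI (Motor performance, upper limb function).** SPADI is the first instrument described under the heading that opens "The motor performance of the upper limb and its functioning will be evaluated on three occasions". It is therefore treated as a function outcome.
- **Content of SPADI (its own section).** The questionnaire "consists of 13 items, five of which address pain and eight of which address function". Only one score is defined: "For the final score, the points are converted into a percentage value (0 to 100"%). No separate pain or function score is named.
- **Pain variable (Pain intensity).** Pain is taken from the VAS: "The intensity of the pain to be considered will be the pain at rest, without movement".

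**The concern.** The purpose of the correlation is to learn whether patients whose pain eases also move and function better. That requires two measures of different things. Total SPADI is a mixture, with 5 of its 13 items (38.5%) about shoulder pain, the same construct that the VAS measures. Higher scores are worse on both instruments, so the overlap pushes the coefficient upwards. A positive and even significant VAS–SPADI correlation could then be reported as a link between pain relief and function when the function items contributed nothing to it.

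At stake is the reading of one secondary correlation. The primary comparison of VAS between arms does not depend on it.

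**Working it through.** The protocol gives no figure for any correlation, so there is nothing of its own to reproduce. The check asks how large a VAS–total SPADI correlation would be if VAS and function were unrelated.

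**Inputs from the document**
- Pain items 5, function items 8, total 13 (SPADI section). If items count equally, the pain weight is w = 5/13 = 0.385.
- Sample size 22 evaluable ("with a combined standard deviation of 1.38, the required sample size was 22 subjects (11 per group")) and 26 enrolled (Sample size section).
- Significance level 0.05. Sidedness is not stated, and two-sided is assumed here.

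**Assumptions (not in the document)**
- Rest VAS correlates 0.6 to 0.8 with the SPADI pain items; this is r_VP.
- Rest VAS correlates 0 with the function items.
- Pain and function items correlate 0 with each other; this is r_PF, varied below.
- The average pain-item and average function-item scores have equal SDs.
- All patients enter a single correlation.

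**Formula.** With zero VAS–function correlation,

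r(VAS, total) = w × r_VP / √(w² + (1 − w)² + 2w(1 − w) × r_PF)

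**Main case, w = 5/13, r_PF = 0.** The formula reduces to r_VP × 5/√(25 + 64) = r_VP × 5/9.434 = 0.530 × r_VP.
- r_VP = 0.6 gives 0.318
- r_VP = 0.8 gives 0.424

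**Sensitivity to the assumptions**

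| Pain weight | r_PF | r_VP = 0.5 | r_VP = 0.7 | r_VP = 0.9 |
|---|---|---|---|---|
| 5/13 | 0 | 0.27 | 0.37 | 0.48 |
| 5/13 | 0.3 | 0.24 | 0.33 | 0.42 |
| 1/2 | 0 | 0.35 | 0.50 | 0.64 |
| 1/2 | 0.3 | 0.31 | 0.43 | 0.56 |

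The rows with weight 1/2 apply only if the total averages two subscale scores. The protocol does not say this, so the 5/13 rows are the ones to rely on.

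**Significance limit.** r_crit = t / √(t² + n − 2), with t the 97.5% point on n − 2 degrees of freedom.
- n = 22: 2.086 / √(4.351 + 20) = 0.423
- n = 26: 2.064 / √(4.260 + 24) = 0.388

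In the main case the expected coefficient reaches these limits when r_VP is 0.423/0.530 = 0.80 (n = 22) or 0.388/0.530 = 0.73 (n = 26).

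**With the eight function items only.** Under the same assumptions the expected correlation is 0, because the pain items have left the score.

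**The other listed outcomes.** For Fugl-Meyer, the protocol uses only the score for upper-half function, not the joint pain domain. Passive range of motion and grip strength are physical measurements. No pain items are described for SSQOL. The overlap is confined to SPADI.

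**The case against.** Four points can fairly be made for the plan.

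1. **The overlap is of construct, not of data.** The pain variable is a separate VAS taken lying at rest and is not a SPADI item, so pain is not literally correlated with itself. This stands, and it is why the size depends on an assumed VAS–pain-item correlation. It does not remove the problem, since two measures of shoulder pain in the same patients would be expected to correlate.

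2. **The size is assumed, and most of the main-case range lies below the limit.** At weight 5/13, only the top of the 0.32 to 0.42 range reaches 0.423 with 22 patients. If pain and function items correlate 0.3, the values fall further. This stands too: overlap alone may come close to significance without reaching it. It still inflates the coefficient that would be reported and interpreted.

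3. **SPADI is one of five measures.** The aim in the Background concerns motor performance, and no rule lets a single SPADI correlation settle it. This limits the consequence and is the main reason to rate the point as minor.

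4. **The composition of SPADI is disclosed, and the reliability cited is for the instrument as it stands.** That is a reason to allow the total alongside the function score. It is not a reason to rely on the total for this question.

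A reader might also infer that Data analysis correlates raw scores with the two arms pooled, which would contradict the aim and create correlation from the treatment difference alone. The document does not support this. Data analysis is silent on score type, visit and handling of arm, and the Background wording points towards changes. A condensed article may leave such details to the full protocol or analysis plan. Sizing a pooling effect would also need a between-arm difference in function, which the document does not give.

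**Conclusion.** The concern holds for SPADI alone. As written, pain will be correlated with a score that is 5/13 pain items and is presented as function, so the coefficient cannot cleanly show that pain relief goes with better function. If rest VAS correlates 0.6 to 0.8 with the pain items and not at all with the function items, the built-in correlation is about 0.32 to 0.42, near the two-sided 5% limit of 0.42 (n = 22) or 0.39 (n = 26). Those limits assume one correlation over all patients, and with fewer patients per correlation they would be higher. That the overlap exists follows from the document; its size does not.

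Severity is minor. The primary outcome, the between-group comparisons and the other four correlations are untouched.

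**What to change.** In Data analysis, replace SPADI in the list of correlates with the eight-item SPADI function score. Total SPADI may be shown beside it if it is labelled as containing five pain items.

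To match the aim in the Background, word the correlations explicitly as change with change, for example: *Change in rest VAS from pre-intervention will be correlated with change over the same interval in the eight-item SPADI function score, Fugl-Meyer upper limb score, SSQOL, passive shoulder range of motion and grip strength.*

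The cost is a change of wording. Each SPADI item is already scored from 0 to 10, so no new data are needed. The downside is slightly lower reliability from 8 items rather than 13, and the reliability cited in the SPADI section may not carry over to the shorter score.
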